#### Baseline characteristics analysis

Among the baseline characteristics of the participants, such as demographic information, continuous data will be presented as means and standard deviations, whereas categorical data will be presented as frequency tables. Continuous data will be compared using the two-sample t-test or the Mann–Whitney test, whereas categorical data will be compared using the χ^2^ test or Fisher’s exact test.

#### Primary and Secondary efficacy outcome analysis

The values of the efficacy outcomes will be presented as descriptive statistics. Differences in the values before and after the interventions will be compared using the paired t-test or Wilcoxon signed-rank test, and a 95% confidence interval will be calculated. The statistical significance of the differences between the experimental and control groups at each assessment point will be determined using a two-sample t-test or Mann–Whitney U test.

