### Randomization and allocation

As this was a multicenter trial, stratified block randomization, with the institution as a stratification factor, will be used to randomly allocate the participants to the experimental and control groups. Randomization will be performed using the SAS 9.4 statistical software (SAS Institute Inc., Cary, NC, USA). A statistician will generate randomization codes, assign serial numbers to all 184 participants, and randomly allocate them to the two groups in a 1:1 ratio to ensure reproducibility. The codes assigned to the participants through randomization will be stored in a double-locked cabinet.

If a participant is deemed eligible after the screening procedure, the investigators will open an opaque allocation envelope containing a piece of paper labeled “experimental group” or “control group” in front of the participant. The investigators will subsequently inform the participants of the allocation results and assigned intervention. Envelopes will be stored separately.

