### Outcome measures

#### Primary outcome measure

An independent researcher will evaluate the outcomes. The schedules are listed in Fig. 2. The primary measurable outcome is the change in the O-SCORAD before (baseline) and after (5 weeks) treatment. O-SCORAD scores are designed to be measured at the screening phase, Visit 1, and Visit 13.

The O-SCORAD excludes subjective symptoms of itching and sleep disturbance from the total SCORAD [10]. A score of 15 to 40 is moderate and 1 to less than 15 is mild.

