#### Safety outcomes analysis

The results of the vital signs and blood tests will be presented as means and standard deviations. Changes in the vital signs and blood test results between the initial and final visits will be compared using the paired t-test or Wilcoxon signed-rank test. The tendency towards the incidence of skin allergies will be tested using the χ^2^ test or Fisher’s exact test.

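### The between-group test does not say whether it compares change or visit scores, omits baseline O-SCORAD and institution, and has no stated confidence interval

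*Protocol article*

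**What the plan says.** The Primary outcome measure section defines the endpoint: "The primary measurable outcome is the change in the O-SCORAD before (baseline) and after (5 weeks) treatment". It adds that "O-SCORAD scores are designed to be measured at the screening phase, Visit 1, and Visit 13", so there is one post-baseline assessment. The Sample size section works from mean 4-week changes of 9.2 (SD 3.73) and 7.2 (SD 3.91) in the earlier study and arrives at 64 per group, raised to 92 for 30% dropout.

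Randomization and allocation specifies "stratified block randomization, with the institution as a stratification factor", in a 1:1 ratio across two hospitals.

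Primary and Secondary efficacy outcome analysis has two inferential sentences. In the first, before/after differences are "compared using the paired t-test or Wilcoxon signed-rank test, and a 95% confidence interval will be calculated". In the second, "differences between the experimental and control groups at each assessment point will be determined using a two-sample t-test" or a Mann–Whitney U test. No covariate is named there or under General principles, and no confidence interval is attached to the second sentence.

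**The concern.** Three things are left loose in the one sentence that carries the trial's efficacy claim.

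- **The tested variable.** The endpoint and the sample size are on change. The before/after difference is assigned to paired tests, and the groups are then compared at each assessment point. A change score does not exist at Visit 1, so the sentence can be read as comparing visit scores. Entry is open to O-SCORAD 10 to 40, so scores at a visit may well be more dispersed than changes, and the two versions of the test could differ greatly in power.
- **Covariates.** Baseline O-SCORAD is measured and institution is stratified on, but neither is used. Precision is given away.
- **Estimation.** The between-group sentence promises significance only. The interval sits with the within-arm change, which in a sham-controlled trial is not the treatment effect. All participants also receive skin-care and diet training and are enrolled on a score, so within-arm improvement can occur without any effect of BMA.

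**Working it through.** **Inputs from the article.** Mean changes 9.2 (SD 3.73) and 7.2 (SD 3.91); 64 evaluable per arm; 30% dropout; two-sided 0.05; entry range 10 to 40.

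**Derived.** Difference = 9.2 − 7.2 = 2.0. Pooled change SD s = √((3.73² + 3.91²)/2) = 3.82.

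**Assumed, because the article does not give them.** Baseline SD b = 7, range 5 to 8.66 (8.66 = 30/√12, a uniform spread over 10 to 40). Correlation between baseline and improvement r = 0.3, range 0 to 0.5.

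**1. The plan's own figure.** n = 2(Zα/2 + Zβ)²σ²/(μ1 − μ2)². Power and σ are not stated. With 80% power and σ = 4, n = 2(1.960 + 0.842)² × 16/4 = 62.8; the t-distribution version gives 63.8, hence 64. With s = 3.82 and 80% power the formula gives 58. Then 64/(1 − 0.30) = 91.4, rounded up to 92. The stated sizes are therefore reproduced under the assumption of σ = 4 and 80% power, and they rest on the SD of change.

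**2. Power of each version of the test** (two-sided t-test, 64 per arm, difference 2.0):

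- SD of the week-5 score = √(b² + s² − 2rbs)
- ANCOVA residual SD = s√(1 − r²)

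| Analysis | SD used | Power |
|---|---|---|
| t-test on change | 3.82 | 83.6% |
| ANCOVA, r = 0 | 3.82 | 83.6% |
| ANCOVA, r = 0.3 | 3.64 | 86.9% |
| ANCOVA, r = 0.5 | 3.31 | 92.4% |
| t-test on week-5 score, b = 5, r = 0.5 | 4.53 | 69.9% |
| t-test on week-5 score, b = 7, r = 0.3 | 6.90 | 37.0% |
| t-test on week-5 score, b = 8.66, r = 0 | 9.47 | 22.0% |

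**3. Second parameterisation.** Take change SD 4 and equal score SDs of 5 to 8 at both visits, so that the correlation between visits is 1 − 16/(2 × SD²), or 0.68 to 0.875. By the normal approximation, power is 80.7% on change, 87.0% down to 83.2% with ANCOVA, and 61.9% down to 29.3% on visit scores. The ordering is the same.

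**4. Omitting institution.** Simulation with score SD 6, change SD 4, 64 per arm, sites balanced within arms and 5,000 runs per cell:

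| Assumed site shift (points) | Change t-test: type I error | Change t-test: power | ANCOVA with baseline and site: type I error | ANCOVA with baseline and site: power |
|---|---|---|---|---|
| 0 | 4.7% | 80% | 4.5% | 84% |
| 2 | 4.4% | 78% | 4.8% | 84% |
| 4 | 2.7% | 73% | 5.0% | 84% |

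The unadjusted test stays below its nominal level and loses power as the sites diverge.

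**5. What a within-arm test can show.** If, purely for illustration, the sham arm changed as the earlier study's comparator did, its paired t at n = 64 would be 7.2/(3.91/√64) = 7.2/0.489 = 14.7. A highly significant before/after result is thus possible in the arm without microneedles.

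**The case against.** The strongest reply is that the analysed variable can be inferred. The endpoint is change, the sample size is on change, and the sentence just before the between-group test speaks of before/after differences. A two-sample test of change at Visit 13 fits all of this, and it is a valid analysis. On that reading ANCOVA adds about 3 power points at r = 0.3 and nothing at r = 0. This stands, and it sets the weight of the point.

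Some stronger readings are tempting, and the article does not support them:

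- **That the trial loses most of its power.** This needs the visit-score reading, which the text neither states nor excludes, and it needs assumed SDs. At the favourable end of the range, power is still 70%.
- **That the unadjusted test is invalid.** It is conservative, and nothing in the article indicates a large difference between two hospitals of the same university.
- **That within-arm tests will be significant in both arms, or will be the basis for efficacy.** The t of 14.7 borrows the change of an active comparator, and a between-group test is planned.
- **That the test will be chosen after seeing the data.** Two tests are named without a selection rule. The rule may be in the analysis plan, which the article says exists.
- **That assessment at each point creates multiplicity for O-SCORAD.** There is one post-baseline visit.

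The unseen plan may also add a between-group interval. The observation here is limited to where the article places the one interval it mentions. Safety testing within arms and the QALY analysis are separate matters for which no harm has been shown, and they are not part of this point.

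**Conclusion.** The point holds as an imprecise and inefficient stated method, not as an invalid one. The article names the between-group test but not its variable, carries neither baseline nor the stratifier into it, and mentions an interval only for within-arm change.

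If change is tested, the cost is small: about 84% power against 84% to 92% with baseline adjustment, plus a loss from ignoring institution that grows with any site difference. If week-5 scores are tested, the cost is large: about 22% to 70%. These figures rest on the earlier study's difference and SDs, 64 evaluable per arm, and a baseline SD and correlation that are assumed. The change is worth making because it removes the ambiguity and costs almost nothing.

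**What to change.** State one primary analysis in advance: ANCOVA of Visit 13 O-SCORAD (or its change) on arm, baseline O-SCORAD and institution, reporting the adjusted between-arm difference with a two-sided 95% confidence interval and p-value. With baseline in the model, the score and the change give the same treatment estimate, so the ambiguity disappears. Keep the rank-based test as a sensitivity analysis. Use the same model, each with its own baseline, for EASI, POEM, DLQI and pruritus VAS. Present within-arm changes descriptively and say that they are not evidence of efficacy.

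The cost is wording in the analysis section and the analysis plan. Baseline scores and institution are already collected, so no visit, measurement or participant is added.

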#### Safety outcomes analysis

The results of the vital signs and blood tests will be presented as means and standard deviations. Changes in the vital signs and blood test results between the initial and final visits will be compared using the paired t-test or Wilcoxon signed-rank test. The tendency towards the incidence of skin allergies will be tested using the χ^2^ test or Fisher’s exact test.

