#### Blood Tests

Blood tests will be conducted at the screening visit and visit 13 to evaluate the general health status of the participants. The examination items will include the aspartate transaminase, alanine transaminase, alanine transaminase, γ-glutamyl transpeptidase, blood urea nitrogen, and creatinine levels. Abnormal values will be reexamined at the discretion of the investigator.

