#### General principles

The safety and full analysis sets (FAS) of this trial will include all the participants who received any intervention at least once after randomization. The per-protocol set will only include participants in the FAS who completed the entire trial without protocol violations. The FAS is primarily used for outcome analysis, although additional outcome analyses of the per-protocol set may be performed. The safety set will be used for safety assessments, including the primary outcome of the trial. Missing values will be handled using the last observation carried-forward method.

Statistical analyses will be performed using SAS (SAS Institute Inc., Cary, NC, USA) or SPSS (IBM Corp., Armonk, NY, USA) softwares for Windows. Statistical significance is set at *p* < 0.025 for a one-tailed test and *p* < 0.05 for a two-tailed test.

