The authors propose a prospective, multicenter, randomized controlled trial (RCT)to evaluate the efficacy, safety, and cost-effectiveness of BMA in patients with moderate or milder AD. The O-SCORAD score will be adopted as the primary outcome measure, while EASI, VAS, POEM, and DLQI scores will serve as secondary outcome measures to enhance the reliability of the results. Additionally, safety, economic evaluation, and gut microbiome analysis will be conducted.

A key limitation of this study protocol is the 5-week evaluation period, which lacks long-term follow-up.While the study can assess short-term improvement following BMA treatment, it remains unclear whether the benefits persist over time. A key strength of this study protocol is that it is the first to evaluate the efficacy, safety, and cost-effectiveness of BMA for managing atopic dermatitis symptoms.

In summary, this multicenter, randomized, sham BMA–controlled study will assess the clinical efficacy and safety of BMA in managing symptoms of moderate or milder AD.

The demand for Korean medicine (KM) therapies in the management and treatment of AD symptoms is increasing. Although the authors developed BMA, there is currently insufficient evidence to support its efficacy and safety in AD treatment. Therefore, a high-quality, multicenter, well-designed RCT is necessary to provide further evidence. This RCT aims to provide evidence that BMA safely improves AD symptoms in patients with sensitive skin while simultaneously assessing its economic feasibility to support broader coverage.

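### Vital signs and blood tests are given only a paired initial-versus-final test, with no BMA-versus-sham comparison, so a change in them cannot be attributed to BMA

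*Protocol article*

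**What the plan says.** The section *Safety outcomes analysis* of the protocol article makes three statements.

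- Summary: "The results of the vital signs and blood tests will be presented as means and standard deviations". Whether the summaries are given by arm is not stated.
- Inference: "Changes in the vital signs and blood test results between the initial and final visits will be compared using the paired t-test", with the Wilcoxon signed-rank test as the alternative. Whether the test is run by arm or pooled is not stated.
- Skin allergies: "The tendency towards the incidence of skin allergies will be tested using the" chi-square or Fisher's exact test.

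The section on primary and secondary efficacy outcomes also starts from paired tests, but then adds a comparison of the arms: "The statistical significance of the differences between the experimental and control groups at each assessment point will be determined using a two-sample t-test", or the Mann–Whitney U test. *Baseline characteristics analysis* likewise names two-sample tests.

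On timing, "Blood tests will be conducted at the screening visit and visit 13", so there is one value before and one after treatment. The safety set in *General principles* takes in everyone treated at least once, in both arms. The Discussion says that the "sham BMA–controlled study will assess the clinical efficacy and safety of BMA".

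**The concern.** A paired test compares participants with themselves, so the randomized control plays no part in it. The article itself describes influences that could move these variables in both arms without any device effect:

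- Everyone receives lifestyle and dietary advice.
- A topical steroid is allowed as rescue.
- Antihistamines may be reduced or stopped during the trial.
- The blood-test baseline is the screening sample, which also serves the liver and renal exclusion limits. Some regression to the mean is therefore possible, though those limits are wide and the effect is probably small.

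Safety is one of the trial's aims. Followed as written, the plan could report a significant laboratory or vital-sign change that has nothing to do with BMA. Where it found no significant change, it would still give no estimate of how BMA differs from sham.

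**Working it through.** The article gives no figure for the safety analysis, so there is none to reproduce. The check has two parts.

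**1. What each section names**

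| Variables | Pre-post test | Between-arm test |
|---|---|---|
| Baseline characteristics | not applicable | two-sample t or Mann–Whitney; chi-square or Fisher |
| Efficacy outcomes | paired t or signed-rank | two-sample t or Mann–Whitney |
| Vital signs, blood tests | paired t or signed-rank | none named |
| Skin allergies | none | chi-square or Fisher (arms not named, but a test for independent groups) |

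The article names group comparisons where it intends them. For vital signs and blood tests it keeps the first step of the efficacy analysis and leaves out the second.

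**2. What the paired test does when BMA has no effect**

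Inputs:

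- n per arm: 64 (the evaluable number in *Sample size*) to 92 (the number randomized, if everyone has a final value).
- Two-sided alpha: 0.05 (*General principles*).
- Common drift d, in SD of the change: **an assumption**, shown from 0 to 0.3.

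Formula: the paired t statistic follows a noncentral t distribution with n − 1 degrees of freedom and noncentrality d√n. At d = 0.2 the noncentrality is 0.2 × √64 = 1.60 for n = 64, and 0.2 × √92 = 1.92 for n = 92.

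| Common drift d | Paired test in BMA arm, n = 64 | n = 92 | Between-arm test of change |
|---|---|---|---|
| 0 | 5.0% | 5.0% | 5% |
| 0.1 | 12.4% | 15.8% | 5% |
| 0.2 | 35.1% | 47.5% | 5% |
| 0.3 | 65.7% | 81.2% | 5% |

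The last column stays at 5% because the expected difference in change is d − d = 0 whatever d is.

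**If the paired test is pooled over both arms**, the problem remains. With equal arms the pooled mean change is ½(d + δ) + ½d = d + δ/2, where δ is the BMA effect. The drift enters in full and the BMA effect is halved.

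**The case against.** The case on the other side has four parts.

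- **Skin allergies.** The same section tests these with a method for independent groups. They are arguably the safety outcome most specific to this device, since the Discussion reports dermal allergic events with metal intradermal needles and none with BMA in the earlier trial. A reader might infer that the sham arm is unused for safety altogether, or that no safety conclusion can be attributed to BMA. The documents do not support that, and the point is limited to vital signs and blood tests.
- **By arm or pooled.** A reader might take the paired tests as arm-by-arm tests whose verdicts are then set against each other. At a drift of 0.2 SD exactly one arm would be significant in 2 × 0.351 × 0.649 = 46% of trials (n = 64) or 2 × 0.475 × 0.525 = 50% (n = 92). But no section states a rule that reads safety from such a split, so these figures are no measure of the plan's error. They also depend on the inputs: at 0.3 SD and n = 92 the figure is 2 × 0.812 × 0.188 = 31%.
- **Multiplicity.** Five distinct analytes in two arms make ten tests, and 1 − 0.95^10 = 40% under independence. That argument concerns the number of tests, not the choice of a paired test. Five between-arm tests would still give 1 − 0.95^5 = 23%. It adds nothing here.
- **Supportive role and the analysis plan.** The blood tests serve to check general health, abnormal values may be re-examined individually, and means and SDs shown by arm would allow an informal comparison. A separate analysis plan exists and may say more.

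The first three parts limit the claim. The fourth lowers the severity but does not remove the point: the article does not leave the method open. It names one, and that method does not compare the arms.

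**Conclusion.** The point holds for vital signs and blood tests only. The one inference stated for them is initial versus final visit, and a change found that way cannot be attributed to BMA rather than to time, advice, rescue use or regression to the mean. This is so whether the test is run by arm or pooled.

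The size depends on a drift that the documents do not give. With no drift the paired test keeps its 5% error rate. At 0.2 SD it gives a significant result in the BMA arm in about 35% to 48% of trials with no device effect. The upper figure assumes a final value for everyone randomized, whereas the article plans for 30% dropout.

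Severity is minor: no primary estimate, sample size or success criterion rests on these variables.

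**What to change.** In *Safety outcomes analysis*, state the BMA-minus-sham difference in change, with a 95% confidence interval, as the comparison for vital signs and blood tests. A baseline-adjusted ANCOVA is preferable; the minimum is the two-sample test already named for efficacy. Present pre-post changes by arm as description, and say in the skin-allergy sentence that the comparison is between BMA and sham.

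The cost is a few lines of text and routine programming. The article describes the same safety assessments for both arms, so no extra data or visits are needed.

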#### Economic outcomes analysis

The QALYs will be calculated using the Area Under the Curve (AUC) method. Treatment costs will be estimated by combining the frequency of each treatment and their unit costs. The economic evaluation will primarily follow the Intention-to-Treat (ITT) principle, which includes all randomized participants, regardless of adherence to the treatment protocol, to assess the effectiveness of the treatments. A secondary analysis will be performed based on the Per-Protocol (PP) principle to evaluate the sensitivity of results to missing data. For missing data in the ITT analysis, the missing data mechanism will be primarily examined using missing diagnosis method, and appropriate imputation method will be applied for building up ITT data before proceeding the analysis. The analysis period will be 8 weeks (the total follow-up period). If additional extrapolation is required, regression models or decision analysis models will be used to estimate costs and effects beyond the follow-up period. After the clinical trial period, the total analysis duration will use the 2024 South Korean currency (KRW) for cost calculations, and a 5% discount rate will be applied, in accordance with the Health Insurance Review and Assessment Service (HIRA) guidelines for cost-effectiveness evaluations. The analysis will be conducted from a societal perspective. In the base-case analysis, representative values (such as mean values) for parameters will be used, while probabilistic sensitivity analysis will be performed using all possible distributions and representative values for the estimated parameters. The results will be presented in tables, including Incremental Cost-Effectiveness Ratios (ICER), Cost-Effectiveness Planes (CEP), Cost-Effectiveness Acceptability Curves (CEAC), and Information Curve values. Statistical analysis for the economic evaluation will be conducted using Stata (MP 16.1) and R (4.3.2), and modeling for extrapolation will be performed using TreeAge Pro(Healthcare version 2023).

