**Fig. 1 Fig1:**
[figure not shown]
CONSORT flow diagram of the study design. This flow diagram illustrates the sequence of participant enrollment, randomization, allocation, follow-up, and analysis in the multicenter, randomized, sham-controlled trial aimed at assessing the efficacy and safety of Biodegradable Microneedle Acupuncture (BMA) for individuals with moderate or milder Atopic Dermatitis (AD). A total of 184 participants will be divided into two groups: the BMA group (*n* = 92) and the Sham BMA group (*n* = 92). Participants will be evaluated at baseline and again at weeks 5 and 8. The diagram also presents the exclusion criteria, instances of loss to follow-up, and the stages of final analysis

This flow diagram illustrates the sequence of participant enrollment, randomization, allocation, follow-up, and analysis in the multicenter, randomized, sham-controlled trial aimed at assessing the efficacy and safety of Biodegradable Microneedle Acupuncture (BMA) for individuals with moderate or milder Atopic Dermatitis (AD). A total of 184 participants will be divided into two groups: the BMA group (*n* = 92) and the Sham BMA group (*n* = 92). Participants will be evaluated at baseline and again at weeks 5 and 8. The diagram also presents the exclusion criteria, instances of loss to follow-up, and the stages of final analysis.

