#### Secondary outcome measure

Secondary outcome measures include the EASI [11], POEM [12, 13], DLQI [14] and VAS [15].

Secondary outcome measures are designed to be measured at Visit 1, and Visit 13.

Human-derived faeces and urine will be collected to determine changes in the gut microbiome before and after treatment. These will be sent to a specializedanalytical laboratory [16].

The timeline for the efficacy evaluation is shown in Fig. 2.

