### Economic evaluation

The author will also conduct an economic evaluation alongside clinical trial to evaluate the cost effectiveness of the study treatment. The utility derived from both treatment groups will be estimated in terms of Quality-Adjusted Life Years (QALYs) using EQ-5D-5 L measurement and the national tariff equation developed in South Korea [17].

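### QALYs are built as an area under the utility curve with no stated adjustment for baseline EQ-5D-5L, so chance baseline differences enter the QALY gain and precision is lost

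*Protocol article*

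**What the plan says.** The Economic evaluation section sets the measure: "The utility derived from both treatment groups will be estimated in terms of Quality-Adjusted Life Years (QALYs) using EQ-5D-5 L measurement", valued with the Korean tariff. The Economic outcomes analysis section then says "The QALYs will be calculated using the Area Under the Curve (AUC) method". The horizon is fixed there too: "The analysis period will be 8 weeks (the total follow-up period"). For the base case the same section says "In the base-case analysis, representative values (such as mean values) for parameters will be used", in contrast to a probabilistic sensitivity analysis that uses distributions. The results feed the ICER, the cost-effectiveness plane and the acceptability curve.

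The section mentions regression only for extrapolating beyond follow-up. It names no covariate for the QALY difference. Elsewhere, the efficacy section compares groups with a two-sample t-test or Mann–Whitney test, also without covariates, although allocation uses "stratified block randomization, with the institution as a stratification factor".

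The EQ-5D schedule cannot be read from the text. The Fig. 1 legend says "Participants will be evaluated at baseline and again at weeks 5 and 8". The Secondary outcome measure section says of the clinical scales "Secondary outcome measures are designed to be measured at Visit 1, and Visit 13". Fig. 2, which holds the schedule, is not shown.

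**The concern.** An AUC QALY contains the participant's baseline utility as one of its terms. If the group difference is a raw difference in mean AUC, part of it is the difference in utility that existed before treatment began, which treatment cannot have caused. Randomisation makes that part zero on average, but not in the one trial that is run.

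Over 8 weeks the attainable gain is small. Even a utility improvement of 0.05 is worth only a few thousandths of a QALY, so a chance baseline difference of ordinary size can be a noticeable share of the ICER's denominator. The article names cost-effectiveness among its aims and in its Discussion links the economic result to wider coverage, so the estimator is worth fixing before data are seen.

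**Working it through.** **Inputs from the document.** Horizon T = 8/52 year. Planned size 92 per group, which reproduces from the Sample size section: 64/(1 − 0.30) = 91.4, rounded up to 92. No stated figure bears on QALY precision.

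**Inputs assumed, because the document gives none.** Equal utility SD at all times; correlation ρ between any two utility measurements 0.5 (range 0.3 to 0.7). For the scale of the effect only: SD 0.15 (range 0.10 to 0.20) and a true utility gain of 0.05 at every follow-up assessment.

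**Step 1: weight of baseline in the AUC (trapezoid rule).**
- Two assessments at the ends of the period: weights 1 and 1, so baseline carries 1/2 = 50%.
- Weeks 0, 5 and 8: weights 5/2 = 2.5, 5/2 + 3/2 = 4, and 3/2 = 1.5, so baseline carries 2.5/8 = 31%.
- Baseline and week 5, with the last value held to week 8: weights 2.5 and 5.5, again 31% for baseline.

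**Step 2: variance with and without adjustment.** With weights w and correlation matrix R, in units of the utility variance, the unadjusted variance is V = w′Rw. The covariance with baseline is C, the first element of Rw. The adjusted variance is V − C².

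At ρ = 0.5:
- Two assessments: V = 3, C = 1.5, adjusted 3 − 2.25 = 0.75, ratio 4.0. In general the ratio is 2/(1 − ρ).
- Weeks 0/5/8: V = 24.5 + 19.75 = 44.25, C = 5.25, adjusted 44.25 − 27.56 = 16.69, ratio 2.65.
- Week 5 held: V = 50.25, C = 5.25, adjusted 22.69, ratio 2.21.

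| Unadjusted/adjusted variance | ρ = 0.3 | ρ = 0.5 | ρ = 0.7 |
|---|---|---|---|
| Two assessments | 2.86 | 4.0 | 6.67 |
| Weeks 0/5/8 | 1.90 | 2.65 | 4.41 |
| Week 5 held to week 8 | 1.63 | 2.21 | 3.61 |

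If the two follow-up values correlate 0.8 with each other, the weeks 0/5/8 ratio at ρ = 0.5 is 2.36. If the SDs differ, the two-assessment ratio at ρ = 0.5 is 5.08 (follow-up SD 0.8 times baseline) or 3.25 (1.25 times baseline). Every case computed favours adjustment.

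**Step 3: size of an ordinary imbalance.** The standard error of the baseline difference is 0.15 × √(2/92) = 0.0221.
- Two assessments: the shift is 0.5 × (8/52) × 0.0221 = 0.0017 QALY, against a true gain of 0.5 × (8/52) × 0.05 = 0.0038, or 44% (29% to 59% for SD 0.10 to 0.20).
- Weeks 0/5/8: the shift is 0.3125 × (8/52) × 0.0221 = 0.0011, against 0.6875 × (8/52) × 0.05 = 0.0053, or 20% (13% to 27%).

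This counts only the baseline term itself, not its carry-over into correlated follow-up values.

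**Step 4: consequence for sign.** The chance that the estimated QALY difference points the wrong way is Φ(−gain/SE). At ρ = 0.5 and SD 0.15:
- Two assessments: SE 0.00295 unadjusted and 0.00147 adjusted, giving 9.6% against 0.5%.
- Weeks 0/5/8: SE 0.00283 and 0.00174, giving 3.1% against 0.1%.

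**The case against.** The strongest reply is that the article never says unadjusted arm means will be compared. The AUC method defines how each participant's QALY is built and is compatible with a later regression on baseline. The sentence on representative values contrasts point estimates with distributions, and a regression-adjusted mean difference is also a mean value. The Statistical analysis section says an analysis plan has been developed, and covariates are often left to such a plan.

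Much of this stands. The text does not rule out adjustment, and a separate plan may already specify it. But the economic section is detailed: it fixes population, perspective, currency year, discount rate and software, and reserves regression for extrapolation. No between-group comparison in the article uses a covariate. An analyst following the text would most naturally compute the raw difference. The point is also not only about silence, because a better estimator is available from data the AUC already requires.

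Two stronger readings are tempting. A reader might infer that the QALY estimate is biased. It is not: under randomisation both estimators are centred on the true gain, and the harm is lost precision and error conditional on the realised imbalance. A reader might also take a fourfold variance as the general result. That needs exactly two assessments, equal SDs and ρ = 0.5, none of which the document states for EQ-5D-5L.

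**Conclusion.** The point holds as an improvement to a secondary, economic analysis. As naturally read, the plan gives an unbiased but needlessly imprecise QALY difference that carries any chance baseline utility difference with weight 50% or about 31%, depending on the schedule. Under equal SDs and assumed correlations of 0.3 to 0.7, the unadjusted variance is roughly 1.6 to 6.7 times the adjusted one. The direction held in every case tried. The size depends on a correlation and an EQ-5D schedule that the document does not show, and the percentage shifts and wrong-sign chances also depend on the assumed SD and gain. The primary O-SCORAD analysis and the 92 per group are not affected.

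**What to change.** In the Economic outcomes analysis section, keep the AUC QALY for each participant, but state that the incremental QALY will be estimated by regressing it on treatment group, baseline EQ-5D-5L utility and institution. Carry the adjusted difference and its uncertainty into the ICER, the cost-effectiveness plane, the acceptability curve and the probabilistic sensitivity analysis. Show raw arm means as description only. If the separate analysis plan already says this, a cross-reference is enough.

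The cost is a sentence or two and one regression in the Stata or R already named. Baseline utility is needed for the AUC anyway and institution is the randomisation stratum, so there are no added visits, measurements or participants.
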